1.To examine whether ultra-protective VT can decrease the all-cause in-hospital mortality rate2.To examine whether ultra-protective VT can reduce the time for successful VA-ECMO weaning (Table 4)3.To examine whether ultra-protective VT is associated with a shorter ICU length of stay4.To examine whether ultra-protective VT is associated with a reduction in interleukin-6 (IL-6), interleukin-8 (IL-8), and monocyte chemotactic protein-1 (MCP-1) levels in broncho-alveolar lavage fluid (BALF)5.To examine whether ultra-protective VT affects respiratory parameters (e.g., total PEEP, plateau pressure [P_plat_], driving pressure [DP], airway resistance [R], static compliance [C_stat_], mean airway pressure [P_mean_], esophageal pressure [P_es_], transpulmonary pressure [P_tp_], and mechanical power [MP]), based on a daily assessment from inclusion to closeout (14)6.To examine whether the ultra-protective VT strategy decreases the lung ultrasound score (LUS) (Figure 1 and Table 5) when assessed daily from inclusion to closeout (15, 16)7.To examine whether ultra-protective VT can lead to an increased analgesic/sedation dosage during the intervention period after inclusion8.To examine whether ultra-protective VT predicts a decrease in the total hospitalization cost9.To examine whether ultra-protective VT is associated with a reduced demand for fluid resuscitation

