### Data collection and management

2.7.

The total duration of ECMO treatment, total time (in days) on IMV, ICU length of stay, analgesic/sedation dosage, all-cause hospital mortality, levels of inflammatory factors in BALF, LUS, amounts of fluid infusion, and total hospitalization cost will be calculated using patient medical records (Table 6).

**Table 6 T6:** Scheduled events and timeline for the ultra-ECMO trial.

		Study period					
Timepoint		Eligibility/Allocation	Post-Allocation			Close-out	
		T0 ECMO initiation	T1 24 h after ECMO	T2 48 h after ECMO	T3 72 h after ECMO	T4 28 days after ECMO	Tx ICU discharge day
Enrollment	Eligibility check	×					
	Informal consent	×					
	Allocation	×					
Intervention	Ultra-protective or protective VT group	×					
Assessments	Demorgraphic data	×					
	Comorbidity	×					
	Clinical characteristics	×					
	Respiratory mechanics parameters	×	×	×	×		
	LUS	×	×	×	×		
	Levels of inflammatory factors in BALF	×	×	×	×		
	In-hospital mortality		×	×	×	×	×
	RASS score	↔					
	VIS	↔					
	Amounts of resuscitative fluids		×	×	×	×	×
	Sedation and NMBA dose	↔					
	ICU LOS	↔					
	Total length of ECMO weaning	↔					
	Total lenght of IMV weaning	↔					
	Total cost for hospitalization						×
	Total hospital LOS	↔					
	28-day VFD	↔					

VT, tidal volume; VFD, ventilator-free day; ICU, intensive care unit; LOS, length of stay, VIS, vasoactive inotrope score; RASS, richmond agitation sedation scal; LUS, lung ultrasound score; BALF, broncho-alveolar lavage fluid.

We will not consider missing values for primary and secondary outcomes during hospitalization. However, missing values could appear specific to patients who survive to hospital discharge. If so, we will contact patients or their next of kin at day 28 to assess the pre-defined outcomes.

Clinical data will include but are not limited to general characteristics (age, sex, weight, height), comorbidities, original disease, the Acute Physiology and Chronic Health Evaluation II score, partial pressure of arterial oxygen/inspired oxygen fraction, PEEP, VT (in ml/kg of PBW), respiratory rate (in breaths/min), DP, P_plat_, P_es_, P_tp_, P_mean_ (in cm of water), C_stat_ (in ml/cmH_2_O), R (in cmH_2_O/L/s), arterial blood PaO_2_ and PaCO_2_ values (in mmHg), and mechanical power (in J/min).

We will also monitor the clinical conditions as well as the ECMO running status and collect any records.

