#### Secondary outcomes analysis

2.9.3.

The intention-to-treat analysis will help in assessing the results of the secondary outcomes. Qualitative secondary outcomes, such as the in-hospital mortality rate in each group, will be reported, and the *χ*^2^ test or Fisher's exact test will be used for the comparison. Quantitative secondary outcomes, such as LUS, will be described in each group in the form of medians with standard deviation values or medians with interquartile ranges, considering the distribution shape, and Student's *t* test or the Mann–Whitney *U* test will support related comparisons between the 2 groups. Stata version 16 (StataCorp LLC, College Station, TX, USA) will assist in carrying out all analyses. A bilateral *p*-value of <0.5 will be used to indicate statistical significance.

Performing an interim analysis will be mandatory in order to check whether there are any inappropriate operations related to data collection or management.

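### ICU stay and ECMO time are tested as raw durations with no account of death, so an arm with more deaths can show a falsely shorter ICU stay

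*Protocol article*

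**What the plan says.** - **Outcomes and direction.** Section 2.2 lists two duration objectives: "To examine whether ultra-protective VT can reduce the time for successful VA-ECMO weaning" and "To examine whether ultra-protective VT is associated with a shorter ICU length of stay". In both, a lower value counts as benefit. Table 2 lists both among the key secondary outcomes.
- **Source of the values.** Section 2.7 takes "The total duration of ECMO treatment, total time (in days) on IMV, ICU length of stay" and other items from the medical records. It adds: "We will not consider missing values for primary and secondary outcomes during hospitalization". No rule is given for a patient who dies on ECMO or in the ICU.
- **Analysis.** Section 2.9.3 opens with "The intention-to-treat analysis will help in assessing the results of the secondary outcomes". It continues with "Quantitative secondary outcomes, such as LUS, will be described in each group", followed by the rule that the Student's t or Mann–Whitney U "test will support related comparisons between the 2 groups". The lung ultrasound score is only an example; durations are not excepted.
- **Mortality.** It enters as a separate comparison: "Qualitative secondary outcomes, such as the in-hospital mortality rate in each group, will be reported", by χ² or Fisher's exact test.

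**The concern.** The patients have refractory cardiogenic shock or cardiac arrest and are on VA-ECMO, and in-hospital death is itself an outcome. Some will die before weaning or ICU discharge. There are two ways to follow the plan as written, and neither answers the stated objective.

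1. **Everyone is kept at the observed duration.** This is the natural reading of intention to treat applied to record-based durations. A death in the ICU ends the stay and is ranked as a short, favourable value. The same holds for total ECMO duration.
2. **Only patients with the event are compared.** Successful weaning does not exist for a patient who dies on ECMO. Leaving those patients out compares groups selected after randomisation, which is no longer intention to treat.

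At stake is the sign of the result on a listed secondary outcome: excess mortality could be reported as a shorter ICU stay.

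**Working it through.** **The plan's own figure.** Section 2.8 gives means 7.1 and 9.2, SDs 8.8 and 9.3, two-sided α 0.05 and 80% power. n = (1.96 + 0.84)² × (8.8² + 9.3²) / 2.1² ≈ 7.85 × 163.93 / 4.41 ≈ 292 per group, as stated. With 5% added, 292 × 1.05 = 306.6, rounded up to 307 per arm, or 614. This concerns ventilator-free days only; it supplies the arm size used below.

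**Inputs.** From the article: 292 per arm, and ECMO and invasive ventilation lasting more than 72 h (section 2.4). Assumed, because the article gives no figures: mortality 50% in one arm and 55% or 60% in the other; survivors' stay averaging 20 days in both arms; deaths after day 3, averaging day 5, 9 or 13, with the same timing in both arms. Only the proportion dying differs. The test level is 0.05, as in section 2.8 (section 2.9.3 prints 0.5, a separate matter).

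**Means.** Mean stay = m × d + (1 − m) × 20, where m is mortality and d the mean day of death. The arms differ by Δm × (20 − d).
- d = 5: 50% gives 0.50 × 5 + 0.50 × 20 = 12.5 days; 55% gives 11.75; 60% gives 11.0. Apparent gain: 0.75 and 1.5 days.
- d = 13: 50% gives 16.5 days; 55% gives 16.15; 60% gives 15.8. Apparent gain: 0.35 and 0.7 days.

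**Simulated Mann–Whitney test** (2,000 replicates; deaths at 3 + gamma with shape 2, survivors at 3 + gamma with shape 4, scaled to the means above). Share of trials in which the higher-mortality arm has a significantly shorter stay:

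| Mean day of death | 50% vs 55% | 50% vs 60% |
|---|---|---|
| 5 | 19% | 52% |
| 9 | 13% | 38% |
| 13 | 7% | 20% |

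Monte Carlo error is about one percentage point. A separate run on the same mean values gave ranges of 8–19% and 18–53%, which are the figures quoted in this point. Without a mortality difference the share is the nominal 2–3%. The t test does not help: at mean day 5 it gives 17% and 47%.

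**A second model.** Take constant hazards and the same discharge hazard in both arms, with latent mean 15 days after day 3. Mean stay is then 3 + 15 × (1 − m): 10.5 days at 50% and 9.0 at 60%. With 307 per arm, the higher-mortality arm is significantly shorter in about 66% of trials, and in about 19–20% at 50% vs 55%.

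**Survivors only.** Under constant hazards the higher-mortality arm still looks shorter, in about 36% of trials at 50% vs 60%. In the gamma model, where survivors' stays are equal by construction, the share is 2–3%, which is chance. The direction depends on the model.

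**The alternative.** With ICU-free days to day 28 and death scored 0, again by Mann–Whitney in the gamma model, the higher-mortality arm is significantly better in 0.2% (55%) and 0% (60%) of trials, and significantly worse in about 17% and 51%.

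**The case against.** **It rests on silence.** Section 2.9.3 does not name the two durations and does not say that deaths enter at their observed time; an article may leave such scoring to the full protocol or analysis plan. This stands in part. However, the article does fix the test for all quantitative secondary outcomes, the analysis population, the raw durations and the direction of benefit. Followed as written, these give the false result.

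**The test is not at fault.** A reader might infer that the Mann–Whitney test cannot be used here. That is too strong: with death scored as the worst value, the same test removes the false benefit. The defect is how the outcome is scored.

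**Stronger readings that the article does not support:**
- That an arm whose patients die sooner is favoured. The calculation varies only the proportion dying, not the timing.
- That time to successful weaning must favour the arm with more deaths. Patients who die have no such time, so this is survivor selection of uncertain direction.
- That sedation dose is biased in the same way. Objective 7 in section 2.2 asks about an increase, and only within the intervention period.

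**The impact is bounded.** These are secondary outcomes, and mortality is reported beside them, so a reader could notice a conflict. This stands, but it does not correct the duration comparison.

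**Conclusion.** The concern holds in this form. For ICU stay, and for ECMO time if taken as total duration, the stated rule can turn excess mortality into a significantly shorter duration. For time to successful weaning, the comparison is confined to selected survivors and its bias has no guaranteed direction.

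The size is illustrative, since mortality, survivor stay and timing of death are all assumed. The false benefit shrinks as deaths come later and approach survivors' length of stay. Deaths are placed after day 3 to respect the >72 h criteria; allowing earlier deaths (mean day 5, about a third before day 3) gives about 15% and 45–48%, within the quoted ranges. The direction for ICU stay does not depend on the exact figures, provided deaths leave the ICU earlier on average than survivors.

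**What to change.** In section 2.9.3, except the two durations from the general rule and adopt one of these:

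- ICU-free and ECMO-free days to day 28, with death scored 0. The planned Mann–Whitney test can stay.
- Cumulative incidence of ICU discharge alive and of successful weaning, with death as the competing event.

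State also that total hospitalization cost will be read only alongside mortality, because death can shorten the period over which cost accrues.

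The cost is a paragraph of wording. Durations and deaths are already collected, and no visit or sample size changes. The price is that ICU-free or ECMO-free days are a composite with death and no longer a plain length of stay; the raw durations can still be reported descriptively, by survival status.

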### Recruitment, randomization, and blinding

2.5.

The Ultra-ECMO trial will include patients who meet the abovementioned eligibility criteria. Formal information about the trial and an official copy of the informed consent form will be sent to their guardians. We will assign participants to an intervention arm or a control arm in a random manner, with those in the former group receiving ultra-protective VT and those in the latter receiving 72 h of protective VT. Guardians will also be informed that they are allowed to drop out of the trial at any time.

The randomization list will be computer-generated according to a simple randomization principle using a ratio of 1:1 by the Clinical Research Board of the School of Public Health of Nanjing Medical University. Participants will be assigned to each group by an independent trial assistant after verification of patient eligibility. Once group allocation has been completed, local investigators will register the record, then reveal the group allocation to care providers, who will deliver the intervention.

Trial assistants responsible for group allocation will be blinded to both groups of patients, but blinding of care providers is impracticable as ventilatory settings and respiratory mechanics measurements are part of routine daily clinical practice. The outcome assessors, data analysts and statisticians will not know the group allocation.

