### Sample size calculation

2.8.

PASS 11 was used for sample size calculation, where a sample size of 292 patients per group would achieve 80% power to detect a difference between the two groups, providing the means were 7.1 and 9.2 with group standard deviations of 8.8 and 9.3 and with a significance level α of 0.05 using a two-sided two-sample *t*-test. Accounting for an anticipated dropout rate of 5%, 614 patients were required for the study.

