#### Primary outcome analysis

2.9.2.

The primary outcome is the 28-day VFD number, which will be determined by the intention-to-treat analysis (ITT) (21), regardless of whether the allocated ventilation strategy was effectively applied or not. The primary outcome will be reported in each group in the form of means with standard deviation values or medians with interquartile ranges. Student's *t* test or the Mann–Whitney *U* test will support related comparisons of the 2 groups while considering their distribution characteristics.

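### Section 2.9.3 sets statistical significance at a two-sided p<0.5, which contradicts the two-sided α of 0.05 used for the sample size and is very probably a slip for 0.05

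*Protocol article*

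**What the plan says.** Three parts of the protocol article bear on this.

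- **Section 2.8, Sample size calculation.** The trial is sized "with a significance level α of 0.05 using a two-sided two-sample" t-test. The section reports that "a sample size of 292 patients per group would achieve 80% power to detect a difference between the two groups". It assumes group means of 7.1 and 9.2, and SDs of 8.8 and 9.3.
- **Section 2.9.2, Primary outcome analysis.** The 28-day ventilator-free day number is compared by Student's t test or the Mann–Whitney U test: the chosen "test will support related comparisons of the 2 groups while considering their distribution characteristics". No significance threshold is given.
- **Section 2.9.3, Secondary outcomes analysis.** After naming the tests for qualitative and quantitative secondary outcomes, the section says that Stata "will assist in carrying out all analyses". The next sentence says that a two-sided p-"value of <0.5 will be used to indicate statistical significance".

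No other threshold appears anywhere in section 2.9.

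**The concern.** A stated decision rule disagrees with the error rate on which the trial was designed. This is not a detail left to a fuller document. The article gives the rule explicitly, and the value it gives is not a usable criterion for significance.

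The rule decides which results are called significant. On the narrow reading it governs the secondary outcomes, including in-hospital mortality. On the wider reading it also governs the primary comparison of a superiority trial. In either case, someone checking the final report against the published plan would find 0.5 in the analysis section and 0.05 only as a sample-size input. If the threshold is corrected only after results are known, the choice of 0.05 could look post hoc, even though it was almost certainly intended from the start.

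**Working it through.** **Inputs (all from section 2.8).** Means 7.1 and 9.2, so the difference is d = 9.2 − 7.1 = 2.1 days. SDs 8.8 and 9.3, so the average variance is (8.8² + 9.3²)/2 = (77.44 + 86.49)/2 = 81.965 and the root-mean-square SD is 9.053. Two-sided α 0.05, power 80%, 292 per group.

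**Step 1. Reproduce the plan's own figure at α = 0.05.**

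n per group = 2 × SD² × (z₁₋α/₂ + z_power)² / d²

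= 163.93 × (1.960 + 0.842)² / 4.41 ≈ 291.8, rounded up to **292**.

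This matches the plan. Power at 292 per group is 80.0% by the normal approximation and 79.9% by the noncentral t. The total after dropout is close too: 584/0.95 = 614.7, against the stated 614.

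**Step 2. Repeat with the threshold as written, α = 0.5.** The critical |z| falls from 1.960 to 0.674.

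n per group = 163.93 × (0.674 + 0.842)² / 4.41 ≈ 85.4, rounded up to **86**.

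The standard error of the difference with 292 per group is √(163.93/292) = 0.749. The standardised difference is 2.1/0.749 = 2.80. Power = Φ(2.80 − 0.674), about **98%**.

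So the stated sample size agrees with 0.05 and not with 0.5.

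**Step 3. Smallest difference declared significant.** This is the critical t on 582 degrees of freedom multiplied by the standard error:

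| Threshold | Critical t | Smallest significant difference |
|---|---|---|
| 0.05 | 1.964 | 1.964 × 0.749 = 1.47 days |
| 0.5 | 0.675 | 0.675 × 0.749 = 0.51 days |

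**Step 4. False-positive rate when there is no true difference.** For a continuous test statistic, the type I error equals the threshold: nominally 50% rather than 5%, a ratio of 0.5/0.05 = 10. A two-sided rule rejects in both directions, so about 25% falls on each side. In 20,000 simulated null trials (292 per arm, t test), 49.96% had p<0.5 and 4.86% had p<0.05. In one given direction, 24.9% had p<0.5. Fisher's exact test, which section 2.9.3 allows, would fall somewhat below nominal because it is discrete.

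**The case against.** The strongest reply is that this is an obvious typographical error. The document itself shows what was meant, because the sample size reproduces at 0.05 and not at 0.5. The same section contains another slip, pairing medians with standard deviations. No analyst or journal is likely to apply p<0.5. That stands as an account of how the error arose and as a limit on the practical harm. It does not make the sentence correct: this is the current text, and nothing elsewhere amends it.

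The second reply concerns scope. The sentence sits under the secondary outcomes heading, and the preceding reference to all analyses describes the use of the software, not the reach of the threshold. One could argue that the primary comparison is governed by the 0.05 in section 2.8. This also stands in part. That the threshold covers the primary outcome is a natural reading, because section 2.9 offers no other, but it is an inference.

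Two stronger conclusions are tempting and are not supported:

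- **That an ineffective intervention would be declared superior half the time.** The 50% is the total over both directions. A false claim in favour of the intervention would occur in about 25% of null trials.
- **That a particular number of secondary findings would be false positives.** Such a count would require assuming that each outcome is tested separately at each time point, which the document does not say. The list of respiratory parameters in section 2.2 is given as examples, not as a fixed set. Nor is an absence of any difference plausible for every outcome: measures such as plateau pressure and mechanical power respond directly to tidal volume.

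**Conclusion.** The point holds as an internal contradiction. The threshold in section 2.9.3 is wrong as written and conflicts with section 2.8 by a factor of ten. No calculation in the plan is at fault: the sample size per group reproduces exactly at 0.05, which is also the best evidence that 0.05 was intended.

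The size of the consequence depends on literal application, which is unlikely. The 50% and 25% figures are nominal rates per comparison and assume no true difference. The figures of 1.47 and 0.51 days assume the planned SDs, 292 patients analysed per group and a t test on the primary outcome.

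A reader might infer that the investigators chose a 50% error rate, or that the primary outcome is definitely bound by it. The document supports neither. It does support that the only decision threshold in the statistical methods is unusable and should be corrected before any results are known.

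**What to change.** In section 2.9.3, change the sentence to a two-sided p-value of <0.05, matching section 2.8. State that this threshold applies to the primary outcome, either in that sentence or in section 2.9.2, so that its scope no longer depends on where the sentence happens to sit.

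This is a one-line correction. It has no operational cost and leaves the sample size unchanged, since 292 per group was already derived at 0.05. How secondary p-values should be treated for multiplicity is a separate question, and this correction does not depend on it.

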## Discussion

3.

In the current guidelines for ARDS, a protective ventilation strategy of limiting VT to 4–6 ml/kg of PBW is recommended, and this approach can reduce the mortality by up to 9% as proved in a randomized clinical trial (22).

Reduced VT is the mainstay of ventilatory management in ARDS, where reductions in driving pressures have been linked to a lower risk of death (23). Several authors have proposed the use of ultra-low tidal volume strategies with VTs of 4 ml/kg of PBW, which can be trialed in patients suffering from ARDS with VV-ECMO or ECCO2R-ECMO (8, 19). Tidal hyperinflation and cyclic recruitment/de-recruitment are important mechanisms leading to ventilator-induced lung injury in patients with ARDS. The mechanical ventilation strategy of ultra-protective VT or protective VT could decrease the transpulmonary driving pressure, stress, and driving pressure, thus alleviating biotrauma, volutrauma, or shearing injury. In past decades, protective mechanical ventilation strategies were extended to patients without ARDS. Fuiter et al. reported that the use of a lung-protective ventilation strategy (6.4 ± 0.8 ml/kg of PBW) in patients with intermediate and high risk levels undergoing major abdominal surgery led to enhanced clinical outcomes as well as less health care use when compared to non-protective mechanical ventilation (11.1 ± 1.1 ml/kg of PBW) (24). Neto et al. also found that ventilation with low VT (<7 ml/kg of PBW vs. ≥7 ml/kg of PBW) led to a lower risk of developing pulmonary complications in patients without ARDS (25). However, similar recommendations are unavailable in patients with refractory cardiogenic shock or CA receiving IMV, and the optimal ventilation strategy in ECMO patients is insufficiently defined (26).

Prior investigation has found that mechanical ventilation with lower VTs (odds ratio, 1.61; 95% confidence interval 1.13–2.28 per a 1-ml/kg of PBW decrease in VT; *p* = 0.008) following OHCA is associated with better neurologic outcomes (5). However, a similar conclusion has not been drawn in in-hospital CA patients (6). In short, it isn't yet confirmed whether ultra-protective VT is also feasible in the specific subject.

In the aspect of pathophysiologic mechanism, ARDS is promoted by an aggressive inflammatory reaction when there is a pulmonary or extrapulmonary assault related to altered alveolar epithelial cells or vascular endothelial cell functions. Comparatively, CPE is a type of pure hydrostatic edema attributable to cardiovascular failure. Irrespective of the pathogenesis, patients with CPE may have similar respiratory mechanics to those found in patients with ARDS (27).

In terms of radiological manifestations, the classical morphological description of an ARDS lung features an decreased amount of sufficiently inflated alveoli and increased amount of poorly inflated alveoli that move from a non-dependent region to a dependent region—namely, the normally aerated lung region, higher-density regions possessing recognizable vessels, and higher-density regions without vessels or bronchi. Analogous to ARDS patients, we also found that some patients with CPE show ARDS-mimic radiologic characteristics (namely, gravity-dependent distribution) (Figure 3).

